### Study drug

Participants will receive D-sorbitol as the active drug and distilled water as the placebo. Participants will rinse with 25 mL of the study drug immediately before taking the sublingual asenapine tablet. Both D-sorbitol and distilled water will be kept clear and colorless to maintain blinding. During the study period, patients will be instructed to rinse their mouths by themselves at home or in the hospital ward. Afterwards, the patients will answer a multiple-choice questionnaire, which will be collected later.

### Experimental schedule

The experimental schedule is shown in Table 1 and Fig. 1. The study will have two groups. Group A will receive D-sorbitol first (test period ① using D-sorbitol and test period ② using placebo solution), and Group B will receive the placebo solution first (test period ① using placebo solution and test period ② using D-sorbitol). There will be a 1-day interval between study periods ① and ②. The study will be conducted in the ward for inpatients and at home for outpatients at the same time of day as the administration of the sublingual asenapine tablets. The participants will provide the following information: disease onset category, duration of illness from the first onset, DSM-5 specific terms, total Positive and Negative Syndrome Scale score at enrollment, sublingual asenapine tablet starting date, asenapine dosage, concomitant medications, comorbidities, smoking history, height, and weight. Before the study, the participants will complete a multiple-choice questionnaire regarding the side effects and duration of getting used to asenapine. Also, after the study is completed, a questionnaire regarding the efficacy of the intervention will be administered.

**Table 1 Tab1:** Experimental schedule

	Experimental schedule				
	Baseline	Experimental period			Discontinuation
Day	Day 0	*Day 1*	*Day 2*	*Day 3*	
Participant background	○				
PANSS	○				
Height, weight	○				
Pre-questionnaire	○				
*Oral rinse with* *D**-sorbitol or placebo*		○		○	
*Post-implementation questionnaire*		○		○	
*Adverse events*					○

*PANSS* Positive and Negative Syndrome Scale

**Fig. 1 Fig1:**
[figure not shown]
Experimental schedule. The study participants will rinse their mouths with 25 mL of D-sorbitol or placebo immediately before taking the sublingual asenapine tablet once a day. All participants will be randomly assigned to Group A or Group B (*n* = 10 each)

### Questionnaire survey content

The pre-questionnaire will ask for a choice-type statement regarding the following items:Length of time to get used to sublingual asenapine tabletsPlease circle the number that applies to how long it takes you to become accustomed to using asenapine sublingual tablets.① No problem from the first time ② A few days ③ One week ④ Two weeks ⑤ One month ⑥ Not used to it yetTime to become accustomed to the taste of sublingual asenapine tabletsPlease circle the number that applies to how long it took you to get used to the taste of asenapine sublingual tablets.① No problem from the first time ② A few days ③ One week ④ Two weeks ⑤ One month ⑥ Not used to it yetPresence or absence of adverse events before and after the use of sublingual asenapine tablets regarding the following items (weight gain, drowsiness, lightheadedness, somnolence, fatigue, insomnia, hand tremors, difficulty moving the body, dry mouth, increased appetite, constipation, dizziness, decreased libido, galactorrhea, menstrual irregularities, and akathisia)

Each question will be rated on a 6-point scale, except for question 3 on the pre-questionnaire.

The post-implementation questionnaires will ask for a choice-type statement regarding the following:Oral conditionPlease describe the condition of your mouth before rinsing today.①Very dry ② Feels dry ③ Normal ④ Concern about saliva ⑤ Very much salivaChange in bitter taste when taking sublingual tabletsHow did you feel the bitterness of this sublingual tablet compared to the bitterness you used to feel?①Almost no bitterness ② Bitterness has been clearly reduced ③ Bitterness seems to have decreased a little ④ No change ⑤ Bitterness has become a little stronger ⑥ Bitterness has become obviously stronger ⑦ Bitterness has become so strong that it is difficult to useWhether the taste of asenapine with the intervention is easy to continueDo you feel that the taste is easy to continue using?①Taste that you can continue to use without any problem ②Easier to continue using than before ③Same taste as before ④Taste more difficult to continue using than before ⑤Difficult to continue usingAll questionnaires will be conducted in Japanese.

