### Participants

Patients attending or hospitalized at the Department of Psychiatry, Nagoya University Hospital, Nagoya, Japan, will be included in the study. The sample size was set as 20 by the following statistical calculation. Using the 7-point Likert scale, we defined 1 to 3 points as improved and 4 to 7 points as non-improved. The McNemar test was used to estimate the sample size for the improved/non-improved binary data. McNemar’s test was used to determine the number of cases required to obtain a significant difference (significance level: 5% two-sided) with more than 90% power in the crossover study. As a result, the number of cases to be analyzed was nine for each group (18 cases in total), assuming a dropout rate of 10%. To reach the target sample size, we will recruit through advertisements at Nagoya University Hospital.

The inclusion criteria are as follows: 1. Adult patients with schizophrenia or psychotic features based on the Diagnostic and Statistical Manual of Mental Disorders, 5th edition (DSM-5), regardless of gender; 2. Patients using sublingual asenapine tablets for more than 2 weeks; and 3. Patients who can provide written informed consent. The exclusion criteria are: 1. Patients with physical diseases or symptoms requiring medical treatment; 2. Pregnant and lactating women; 3. Patients with a history of convulsions; 4. Patients with a substance use disorder; 5. Patients with a taste disorder; 6. Patients with an olfactory disorder; 7. Patients who cannot understand the questionnaire protocol; and 8. Other patients whose inclusion in the study is deemed inappropriate by the attending physician. We will interview participants to determine if they meet these exclusion criteria. The reason for excluding olfactory disorder is that an associations between olfactory and bitter taste receptors has been suggested, and olfactory disorder may also affect the evaluation of taste [11]. The discontinuation criteria are: 1. If the research participant requests discontinuation; and 2. If the attending physician determines that there will be a clear disadvantage in the participant’s disease.

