### Secondary outcome

The secondary end point will be the willingness to continue asenapine, subjectively self-rated on a 5-point scale, which addresses post-implementation question 3. The use of mouthwash before taking asenapine is expected to reduce its bitterness. There is expected to be a need to evaluate whether the reduction of bitterness affects adherence to asenapine.

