### Statistical analysis

The primary endpoint was evaluated on a 7-point Likert scale, with 1 to 3 points defined as improvement and 4 to 7 points as non-improvement. The secondary endpoint was evaluated on a 5-point Likert scale, with 1 to 2 points defined as improvement and 3 to 5 points as non-improvement. The difference in population proportions for improved/non-improved binary data will be analyzed using a McNemar test. Participants with missing data will be excluded from the analysis, and no interim analyses will be performed.

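### On the ease-of-continuing item (post-question 3), a patient with no taste problem and no change can truthfully choose two options that are coded oppositely; the bitterness item shares the form but is better protected

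*Protocol article*

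**What the plan says.** The article prints the response options under Questionnaire survey content and the coding under Statistical analysis.

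- **Post-question 3 (secondary endpoint).** The stem asks only whether the taste is easy to keep using and makes no comparison with the past. The options begin "①Taste that you can continue to use without any problem ②Easier to continue using than before ③Same taste as before". Option 4 is again a comparison with before. The coding is "with 1 to 2 points defined as improvement and 3 to 5 points as non-improvement".
- **Post-question 2 (primary endpoint).** The stem asks for a comparison with the bitterness felt previously. The options begin "①Almost no bitterness ② Bitterness has been clearly reduced ③ Bitterness seems to have decreased a little ④ No change". The coding is "with 1 to 3 points defined as improvement and 4 to 7 points as non-improvement".
- **Who is enrolled.** Under Participants the treatment criterion is "Patients using sublingual asenapine tablets for more than 2 weeks". No listed criterion requires bitterness or trouble with the taste.
- **What is known beforehand.** The pre-questionnaire asks "how long it took you to get used to the taste of asenapine sublingual tablets.① No problem from the first time" and goes on to longer periods. As printed, it does not record the current level of bitterness or of ease of continuing.
- **The label.** Under Secondary outcome: "The secondary end point will be the willingness to continue asenapine, subjectively self-rated on a 5-point scale".

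**The concern.** A binary improved/non-improved split is only as sound as the options feeding it. On question 3, one true state (tolerated before, nothing has changed) fits both option 1 and option 3, and these fall on opposite sides of the cut. The code then depends on which true statement the patient happens to pick.

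Three consequences follow.

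1. If such patients pick option 1 both times, the improvement rates on D-sorbitol and on water both rise although nothing improved.
2. If they pick option 1 once and option 3 once, they create a discordant pair that carries no information.
3. A tolerant patient who ticks option 1 after water is already coded improved. That patient cannot register as better after D-sorbitol, even if the taste really is easier then.

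Separately, the result would be reported as willingness to continue asenapine, while the item asks about the ease of continuing with the taste.

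**Working it through.** **Reading the options against the coding**

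| Item | Stem | Option 1 | Unchanged option | Code of option 1 / unchanged option |
|---|---|---|---|---|
| Question 3 | not comparative | level | 3 | improved / non-improved |
| Question 2 | comparative | level | 4 | improved / non-improved |

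On question 3 nothing in the stem steers an unchanged, tolerant patient from 1 to 3. On question 2 the stem asks for a comparison, so the no-change option is the natural answer for such a patient.

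**The plan's own figure.** The sample size is 18 analysed with 10% dropout: 18 / 0.9 = 20, as stated. The 18 itself cannot be reproduced, because no discordant-pair rates are given. The rates below are therefore assumptions. The calculation was made for the improved/non-improved split of the 7-point scale; no power is stated for question 3.

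**Test used here.** Exact two-sided McNemar at 5% (the exact version is my choice). With b pairs improved on D-sorbitol only and c on placebo only, p = min{1, 2 × P[Bin(b+c, 0.5) ≥ max(b, c)]}.

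**(a) Consistent option-1 answers.** Take b = 8 and c = 1 among 18. Then p = 2 × (9 + 1) / 2^9 = 20 / 512 = 0.039. Now let k of the concordant patients tick option 1 both times, with the other concordant patients coded non-improved both times.

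| k | Improved on D-sorbitol | Improved on placebo | Difference | p |
|---|---|---|---|---|
| 0 | 8/18 = 44% | 1/18 = 6% | 7/18 | 0.039 |
| 3 | 11/18 = 61% | 4/18 = 22% | 7/18 | 0.039 |
| 6 | 14/18 = 78% | 7/18 = 39% | 7/18 | 0.039 |

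The rates move; the paired difference and the test do not.

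**(b) Inconsistent answers.** Assume that patients with something to improve have discordant probabilities 0.60 (D-sorbitol only) and 0.05 (placebo only). Let k of the 18 be no-problem patients.

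- *Consistent:* they are always concordant, so power comes from the other 18 − k patients.
- *Random:* each picks option 1 or 3 with probability 0.5, independently in each period. The chance of a false discordant pair is 0.5 × 0.5 = 0.25 in each direction. A probability of 0.5 gives the most false discordance under independent choice, since 2π(1−π) is largest there.

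Power is the summed probability of all (b, c) with b > c and p ≤ 0.05. The smallest significant splits are 6–0, 8–1 and 10–2.

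| k | Expected false discordant pairs (random) | Power, consistent | Power, random | Loss from ambiguity |
|---|---|---|---|---|
| 0 | 0 | 0.865 | – | – |
| 3 | 1.5 | 0.770 | 0.660 | 0.11 |
| 6 | 3 | 0.611 | 0.412 | 0.20 |

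If each patient instead has chance k/18 of being a no-problem patient, the figures are 0.761 and 0.655 for k = 3, and 0.591 and 0.422 for k = 6. The picture is the same.

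Only the last column belongs to the ambiguous options. The fall from 0.865 to 0.770 or 0.611 arises because those patients have nothing to improve. It would be the same if they ticked the unchanged option after both rinses.

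**The case against.** **Question 2 is protected.** This largely stands. The item is presented as a change in bitterness, its stem is comparative, and it has a no-change option. In that frame option 1 can be read as the top grade of reduction. A reader might infer that the primary endpoint is miscoded just as the secondary is. The text does not support that; it shows only that this is possible.

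**The McNemar test is not biased.** This stands for consistent answers, as shown in (a). A reader might infer that the coding favours D-sorbitol. The article gives no reason why an unchanged patient would lean to option 1 after one solution. Participants may tell the liquids apart by sweetness, but they are not told which is placebo. If the choice does not depend on the solution, false discordance is symmetric and costs power rather than creating an effect.

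**Power is lost by enrolling patients with nothing to improve, whatever the coding.** This also stands. It would be wrong to charge that whole loss to the coding, and rewording would not recover it.

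**The number of such patients is unknown.** True. More than two weeks of use does not imply absence of bitterness, and the pre-questionnaire also allows for patients not yet used to the taste. Its first option shows only that the plan foresees some patients without a taste problem. The counts of 3 and 6 are illustrations.

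**The forms are in Japanese.** The contrast between level and change is read from the English rendering and should be checked against the form in use.

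**The wording of question 3 is printed, so the label misleads nobody.** Only partly: results tend to be cited by the endpoint's name, and the Secondary outcome section links it to adherence.

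**Conclusion.** The point holds for question 3. Two options are true of the same unchanged patient, and the stated rule codes them oppositely. For question 2 the same form creates a possibility of misclassification and no more.

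The effect is inflated improvement rates on both solutions when answers are consistent, and lost power when they are not. In the illustration the ambiguity costs about 0.11 of power with 3 no-problem patients and about 0.20 with 6. These figures rest on assumed discordant rates of 0.60 and 0.05, on 18 analysed patients, on the exact test and on random choice between the two options. The article supplies only the 18.

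The name of the secondary endpoint also goes beyond the question asked. Severity is moderate, and mainly concerns the secondary endpoint.

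**What to change.** **Before forms are used.** Word option 1 as a change on both items, and check the result against the Japanese form:
- question 3: *Much easier to continue using than before*;
- question 2: *Bitterness has almost disappeared compared with before*.

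**If forms are already in use.** Keep the stated coding for the main analysis. Add a sensitivity analysis that leaves out patients who chose the first pre-questionnaire option for getting used to the taste. Do not recode option 1 as non-improved for them. That item measures how long it took to get used to the taste, not whether bitterness was felt. Recoding would also make answer 1 non-improved while the weaker positive answers (2 and 3 on question 2, 2 on question 3) stay improved. For the same reason the sensitivity analysis is only a partial remedy.

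**In either case.** Report question 3 as ease of continuing with the taste, not as willingness to continue asenapine.

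**Cost.** Two reworded options, or one extra analysis using an item already collected, and a changed label. Reported improvement percentages may be lower on both solutions, and the sensitivity analysis has fewer patients.

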### Primary outcome

The primary end point is the taste evaluation of bitterness, which addresses post-implementation question 2. The participants will self-assess on a 7-point scale regarding the use of D-sorbitol and the reduction of the bitter taste.

### Secondary outcome

The secondary end point will be the willingness to continue asenapine, subjectively self-rated on a 5-point scale, which addresses post-implementation question 3. The use of mouthwash before taking asenapine is expected to reduce its bitterness. There is expected to be a need to evaluate whether the reduction of bitterness affects adherence to asenapine.

### Statistical analysis

The primary endpoint was evaluated on a 7-point Likert scale, with 1 to 3 points defined as improvement and 4 to 7 points as non-improvement. The secondary endpoint was evaluated on a 5-point Likert scale, with 1 to 2 points defined as improvement and 3 to 5 points as non-improvement. The difference in population proportions for improved/non-improved binary data will be analyzed using a McNemar test. Participants with missing data will be excluded from the analysis, and no interim analyses will be performed.

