**Methods:**

In this single-blind, placebo-controlled, crossover trial, we plan to recruit 20 adult patients with schizophrenia spectrum disorder who take sublingual asenapine tablets. The participants will be divided into two groups (*n* = 10 each). Each group will be given a D-sorbitol or placebo solution on the first day for rinsing before taking the sublingual asenapine tablets. After a 1-day interval, the participants will rinse their mouths again with a different liquid. Questionnaires regarding changes in taste and the willingness to continue asenapine will be conducted before the start of the study and after each rinse. The primary and secondary end points will be a taste evaluation of bitterness, and the willingness to continue asenapine, respectively. Differences in questionnaire scores between the D-sorbitol and placebo solutions will be calculated and analyzed using a McNemar test.

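### Cutting the 7-point bitterness rating to improved versus non-improved for McNemar is valid and consistent but inefficient for about 18 pairs; a paired ordinal primary analysis is a cheap improvement

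*Protocol article*

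**What the plan says.** The Primary outcome section defines the endpoint on the full scale: "The participants will self-assess on a 7-point scale regarding the use of D-sorbitol and the reduction of the bitter taste". The Statistical analysis section then cuts it: "The primary endpoint was evaluated on a 7-point Likert scale, with 1 to 3 points defined as improvement and 4 to 7 points as non-improvement". Next comes the test: "The difference in population proportions for improved/non-improved binary data will be analyzed using a McNemar test".

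The Participants section uses the same split ("Using the 7-point Likert scale, we defined 1 to 3 points as improved and 4 to 7 points as non-improved") and the same test ("The McNemar test was used to estimate the sample size for the improved/non-improved binary data"). It claims more than 90% power at a two-sided 5% level, and says "the number of cases to be analyzed was nine for each group (18 cases in total), assuming a dropout rate of 10"%. Twenty patients are to be recruited. No expected proportions are given.

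The Methods paragraph of the abstract reads: "Differences in questionnaire scores between the D-sorbitol and placebo solutions will be calculated and analyzed using a McNemar test". It does not mention the cut.

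In the Questionnaire survey content section, the bitterness question asks for a comparison with the bitterness the patient used to feel. Category 4 means no change. Categories 2, 3, 5, 6 and 7 describe degrees of change, but category 1 describes a level, namely hardly any bitterness.

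**The concern.** McNemar's test draws information only from patients who fall on different sides of the cut under the two solutions. Each solution is scored against memory, not against the other solution. Any benefit of rinsing as such, or of expectation, can therefore move a water rating to 3. The Secondary outcome section expects mouthwash use before asenapine to reduce bitterness and does not confine this to D-sorbitol. A patient who scores water 3 and D-sorbitol 1 shows the extra masking the trial is looking for, yet counts as concordant and drops out of the test.

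With about 18 analysed patients there is little information to spare. A real advantage of D-sorbitol over water could be missed although the ratings that show it have been collected. The abstract adds a smaller problem: a difference in scores is not a quantity that McNemar analyses, so its sentence cannot be carried out as worded.

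**Working it through.** **1. The plan's own figure.** Inputs from the Participants section: 18 analysed, 10% dropout, two-sided 5%, power above 90%.

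Dropout: 18 / (1 − 0.10) = 20, which agrees with the recruited number.

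The 18 itself can only be back-solved, because no discordant proportions are stated. Let p10 be the proportion improved on D-sorbitol only, p01 the proportion improved on water only, ψ = p10 + p01 and d = p10 − p01. Then

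N = (1.96·√ψ + 1.28·√(ψ − d²))² / d².

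For p10 = 0.60 and p01 = 0.05: ψ = 0.65, d = 0.55, N = (1.580 + 0.755)² / 0.3025 = 18.0.

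| p10 / p01 (assumed) | N by formula | Exact McNemar power at 18 | Uncorrected power at 18 |
|---|---|---|---|
| 0.60 / 0.05 | 18.0 | 87% | 92% |
| 0.50 / 0.02 | 19.2 | 86% | 93% |
| 0.45 / 0.001 | 19.0 | 89% | 98% |
| 0.70 / 0.10 | 18.8 | 83% | 89% |

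The stated size is therefore reachable with McNemar, but it presupposes a net responder difference of about 45-60 percentage points.

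**2. Tests compared at 18 pairs.** Let b and c be the two discordant counts.
- Uncorrected McNemar rejects if (b − c)² / (b + c) > 3.84.
- Exact McNemar uses p = 2·P(Bin(b + c, ½) ≤ min(b, c)). It needs at least six discordant pairs: 2 × 0.5⁶ = 0.031, whereas 2 × 0.5⁵ = 0.0625.
- The signed-rank test ranks the absolute within-patient score differences and uses their signs.

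**3. Assumptions, none from the documents.** Latent-normal scores are cut into seven categories, with within-patient correlation 0.5 and a D-sorbitol shift in latent SD units. The 20% row of the water distribution is 3, 5, 12, 55, 15, 7 and 3% for categories 1 to 7. There were several thousand simulated trials per setting.

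| Improved on water | Shift (SD) | Exact McNemar | Uncorrected McNemar | Signed-rank | Loss, exact | Loss, uncorrected |
|---|---|---|---|---|---|---|
| 20% | 0.75 | 30% | 47% | 71% | 41 | 24 |
| 40% | 0.75 | 34% | 51% | 76% | 42 | 25 |
| 20% | 1.0 | 58% | 75% | 92% | 34 | 17 |
| 33% | 1.0 | 62% | 76% | 95% | 33 | 19 |
| 40% | 1.0 | 59% | 74% | 95% | 36 | 21 |
| 50% | 1.0 | 53% | 71% | 94% | 41 | 23 |
| 20% | 1.25 | 83% | 91% | 99% | 16 | 8 |
| 40% | 1.25 | 80% | 90% | 99.5% | 20 | 9 |
| 50% | 1.25 | 71% | 87% | 99% | 28 | 12 |

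The signed-rank test is exact in the 33% and 50% rows and in the 20% rows at 0.75 and 1.0 SD; elsewhere it is the normal approximation. Over 20-50% improved on water and shifts of 0.75-1.0 SD, repeated runs put the loss at about 16-28 points (uncorrected) and 32-47 points (exact). With no effect, the exact signed-rank test rejected in 3-4% of trials, so the gain does not come from an inflated error rate.

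The reason shows in the discordant counts. At a 1.0 SD shift with 20% improved on water, p10 is about 0.397 and p01 about 0.033, so 18 × 0.430 ≈ 7.7 discordant pairs are expected, close to the exact test's minimum of six. In sample-size terms, at a 1.25 SD shift the signed-rank test reaches 90% power with about 11 pairs and uncorrected McNemar with about 18.

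**4. The case with no loss.** Suppose every water rating is 4 and D-sorbitol ratings fall only in 1-4. Every non-zero difference then has the same sign, and both exact tests give p = 2 × 0.5ᵐ for m improved patients, so they coincide. With 40% improved on D-sorbitol, power is 79% (exact McNemar), 97% (uncorrected McNemar) and 91% (signed-rank, normal approximation).

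**The case against.** The cut is prespecified, lies exactly at no change, and is the same in the Participants and Statistical analysis sections. It is a natural responder definition, and McNemar is a valid paired test for it. All of this stands, and nothing here points to bias or a type I error problem.

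A reader might infer from the abstract that the plan holds two competing primary analyses. The documents do not support that: the abstract names McNemar too, and no other test appears anywhere. What is left is loose wording about the quantity compared.

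A reader might also take a large power loss as established. It is not. The documents give no score distribution, correlation or discordant proportions, and do not say whether the exact form of McNemar will be used. The loss is much smaller where McNemar already has about 90% power, and can be nil.

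Two further points have force. Category 1 is a level while the others are changes, so the seven categories are not strictly one change scale, and ranking score differences treats the steps as comparable. And a water 7 / D-sorbitol 4 pair, which the cut also discards, is a weak argument for the full score, because that patient reports no reduction with D-sorbitol. The water 3 / D-sorbitol 1 pair remains, and there the cut discards the comparison of interest.

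**Conclusion.** The point holds as one of efficiency and is best treated as a cheap improvement. The planned analysis is valid and internally consistent, but it leaves collected information unused in a trial of about 18 pairs. How much that costs rests entirely on the assumptions shown: substantial for moderate shifts with some improvement on water, modest for the large effects the sample size presupposes when few patients improve on water, and none in the limiting case of step 4. The claim of more than 90% power does not settle the matter, since the effect behind it is not stated. The abstract's wording is a separate, minor correction.

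**What to change.** - Make the primary analysis a paired ordinal comparison of the 7-point score. The preferred form takes each patient's period 1 minus period 2 difference and compares Groups A and B with an exact rank-sum test, which also allows for a period effect. A signed-rank test on within-patient differences is the simpler alternative.
- Keep the 1-3 versus 4-7 McNemar comparison as a supportive responder analysis.
- Note that category 1 is worded as a level and not as a change.
- State in the Participants section that the sample size was derived for the McNemar comparison.
- Reword the abstract so that the quantity it describes is the one its test analyses.

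No new patients or data are needed. The costs are that the responder percentage is no longer the headline result, and that the wording of a registered, board-approved protocol has to be amended before the data are analysed.

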## Methods

### Study design

The purpose of this single-blind, placebo-controlled, crossover study is to evaluate the efficacy of D-sorbitol in masking the bitter taste of sublingual asenapine tablets. D-Sorbitol oral solution 75% (KOWA, Aichi, Japan) will be used as the test solution in this study. The dosing period will be 1 day each in study periods ① and ②. Taste evaluations will be performed at home for outpatients and during hospitalization for inpatients, with a 1-day test interval to eliminate the carryover effect of D-sorbitol. Patients will be given an oral rinse with D-sorbitol or a placebo solution before taking the sublingual asenapine tablets. Then, after a 1-day interval, the patients will rinse their mouths again with a different liquid than that used on day 1. A questionnaire survey regarding taste evaluations and the intention to continue asenapine with the intervention will be conducted on the participants before the start of the study and after each rinse.

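### The planned McNemar test pools the two randomised sequences and ignores period: if a period effect exists it loses power, and unequal groups add a small bias

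*Protocol article*

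**What the plan says.** The design is a two-sequence, two-period crossover with 10 patients per sequence (Fig. 1). Under Experimental schedule, "Group A will receive D-sorbitol first (test period ① using D-sorbitol and test period ② using placebo solution"; Group B takes the two solutions in the reverse order.

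Under Statistical analysis, both the 7-point bitterness rating and the 5-point continuation rating are cut into improved/non-improved. The resulting "binary data will be analyzed using a McNemar test". The abstract names the same test ("will be calculated and analyzed using a McNemar test"), and the Participants section uses it for the sample size.

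The only provision between the two test days is under Study design: "with a 1-day test interval to eliminate the carryover effect of D-sorbitol". No section mentions period or sequence in the analysis. Participants with missing data are excluded.

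**The concern.** McNemar's test compares the number of patients improved only on D-sorbitol with the number improved only on placebo, in one table for all patients. Whether D-sorbitol came first or second plays no part. Any general shift between Day 1 and Day 3 therefore produces discordant pairs that favour placebo in one group and D-sorbitol in the other. In equal groups these cancel in the estimate but remain in the test as noise. In unequal groups they do not fully cancel, and part of the period effect is reported as a treatment effect.

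A washout interval deals with residual D-sorbitol, which is a different problem. A period effect is plausible, though not shown. The rating is a subjective comparison with remembered bitterness (Questionnaire survey content). The Day 3 rating follows one earlier rinse and rating, and the article accepts that patients can tell the liquids apart by sweetness (Randomization and blinding).

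At stake are the power of a trial with 18 analysed patients and a stated target above 90%, and to a lesser degree the size of the reported difference. The article itself fixes the test, so this is not a detail left to an analysis plan.

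**Working it through.** **The plan's own figure.** The dropout step reproduces: 18/(1 − 0.10) = 20. The 18 cannot be checked, because no improvement rates or discordant proportions are given. It is attainable: with 60% improved on D-sorbitol only and 5% on placebo only, the discordant proportion is 0.65, the difference is 0.55, and N = [1.96√0.65 + 1.2816√(0.65 − 0.55²)]²/0.55² ≈ 18.0.

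**Bias of the pooled difference.** Let τ be the treatment difference and π the period-2-minus-period-1 difference in the proportion improved. The D-sorbitol-minus-placebo difference is then τ − π in Group A and τ + π in Group B. Pooling gives

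[n_A(τ − π) + n_B(τ + π)]/(n_A + n_B) = τ + π(n_B − n_A)/(n_A + n_B).

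The bias is zero in equal groups. With 10 randomised per group, 18 analysed patients can only split 9/9 or 10/8, so the largest factor at that size is 2/18.

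**Assumed model (none of it from the documents).** Latent ratings are normal with SD 1 and within-patient correlation 0.5; a patient is improved above a cut-point of 0.5 SD; D-sorbitol adds 1.5 SD; period 2 adds a shift towards improvement. Without a period effect, placebo gives Φ(−0.5) = 30.9% improved and D-sorbitol Φ(1.0) = 84.1%.

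**Bias at 10/8, with π taken at the placebo level:**
- 0.25 SD: π = 40.1 − 30.9 = 9.2 points; × 2/18 = 1.0 point
- 0.5 SD: π = 50.0 − 30.9 = 19.1 points; × 2/18 = 2.1 points
- 1 SD: π = 69.1 − 30.9 = 38.2 points; × 2/18 = 4.2 points

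The sign depends on which group is smaller.

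**Power at 9/9, two-sided 5%.** Prescott's test classifies each patient as improved in period 1 only, in period 2 only, or tied, and compares Groups A and B on those scores, with the margins held fixed.

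| Period shift | Exact McNemar | Exact Prescott | Gap |
|---|---|---|---|
| none | 93.9% | 94.1% | 0.2 |
| 0.25 SD | 92.0% | 92.4% | 0.4 |
| 0.5 SD | 88.5% | 89.8% | 1.3 |
| 1 SD | 71.0% | 79.3% | 8.3 |

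These are simulated values; full enumeration under the same model agrees with each to within one percentage point.

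**Power at 10/8.** With no period effect it is 94.1% v 95.2%. If Group B is the smaller, a 0.5-SD shift gives 85.6% v 92.7% (gap 7.1) and a 1-SD shift 63.8% v 85.1% (gap 21.3). If Group A is the smaller, the bias runs in favour of D-sorbitol and the gaps shrink to about 1 and 6 points. Over repeated simulations the upper ends are 6 to 7 points at 0.5 SD and 21 to 22 at 1 SD.

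**Second model, on the proportion scale.** With τ = 0.5 at 9/9, asymptotic McNemar v Prescott is 87.2% v 87.7% at π = 0, 87.6% v 89.1% at 0.1, 78.2% v 83.1% at 0.2 and 71.5% v 78.9% at 0.3. Assumed discordance is 0.6, 0.6, 0.7 and 0.8 in turn.

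**Type I error.** In the second model, with τ = 0 and discordance 0.4, asymptotic McNemar at 9/9 rejects in 4.4% of trials at π = 0, 3.5% at 0.2 and 2.4% at 0.3. Its highest rate in any null scenario, unequal groups included, was 4.9%.

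**The case against.** The strongest reply is that counterbalancing already handles period. With equal randomised sequences the pooled difference is unbiased under an additive period effect, and the test is conservative, not liberal. That stands. A reader might infer that ignoring period risks a false positive; no null scenario run shows inflation.

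Second, the period effect is hypothetical. The documents neither give nor rule one out. Patients have used asenapine for more than two weeks, the two ratings are two days apart, and both refer to earlier bitterness. A 1-SD shift is large beside a 1.5-SD treatment effect. This also stands, and up to 0.5 SD in equal groups the loss is only 0.4 to 1.3 points. It limits the size of the point, not its direction. Contrast with the first rinse, one possible mechanism, is also close to carryover, which Prescott's test does not remove.

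Third, a reader might infer a large bias from very lopsided groups. Neither group can contribute more than 10 patients, and with 18 analysed the most uneven split is 10/8. Heavier loss, such as 10/6, would widen the bias (5 points at π = 0.2, since 0.2 × 4/16 = 0.05), but it exceeds the planned dropout.

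Fourth, part of the fall in McNemar power with a growing period effect is shared by Prescott's test (94.1% to 79.3% at 9/9). Only the gap between the tests is due to ignoring period. Any gain from keeping the ordinal score is a separate matter from period and is not counted here.

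**Conclusion.** The point holds as a worthwhile improvement to the primary and secondary analyses. The chosen test discards the randomised order, and the 1-day interval does not make up for that. If there is no period effect, nothing is lost. If there is one, the harm is lost power: about 0.4 to 8 points at 9/9 for shifts of 0.25 to 1 SD, and at 10/8 about 1 to 7 points at 0.5 SD and 6 to 22 at 1 SD. At 10/8 there is also a bias of about 1 to 4 points, against an assumed treatment difference of 84.1 − 30.9 = 53.2 points.

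That McNemar pools the sequences follows from the text. The magnitudes rest wholly on the assumed treatment shift, correlation, cut-point and period shift. The documents do not support saying that a period effect is present, that the planned test is invalid, or that the estimate is biased when the groups stay equal.

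**What to change.** In the Statistical analysis section, replace McNemar's test for both binary endpoints with Prescott's exact test by randomised group: improved in period 1 only, in period 2 only, or tied, tabulated for Group A against Group B.

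Estimate the treatment effect as half the difference between groups in mean period difference (period 1 minus period 2). In the notation above this is ½[(τ − π) − (−τ − π)] = τ, whatever the group sizes. Report results by sequence so that readers can see any period effect. Change the abstract to match.

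Name Prescott's test explicitly. In a separate logistic simulation at 9/9 with period effects, the Fisher form of the Mainland-Gart test, another period-adjusted option, had less power than exact McNemar (81% v 89% and 58% v 78%), while Prescott's had more (95% and 92%).

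The cost is one sentence and no extra patients or data. There is no power loss at 9/9 or 10/8 without a period effect. With heavier, uneven loss the price is small: at 10/6 with no period effect, 81.6% for Prescott against 82.6% for asymptotic McNemar.
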